## Abstract

**Background:**

Research has consistently demonstrated that preventive cardiology programs have limited success, and healthy practices among high-risk individuals remain suboptimal. Furthermore, there are no current programmes in Malta that offer support to first-degree relatives of patients with premature coronary heart disease. This internal pilot study will determine the feasibility, acceptability, and potential effectiveness of a preventative intervention.

**Methods/design:**

We are conducting a 12-month single-centre, two-armed group randomised controlled trial (RCT), recruiting a sample of 100 asymptomatic first-degree relatives of patients with premature coronary heart disease (CHD). The study seeks to test an evidence-based intervention to reduce modifiable risk and determine its feasibility and acceptability. The Intervention will be delivered at an outpatient office based in a large acute academic hospital. It will comprise risk communication using an online risk calculator, a counselling style adapted from motivational interviewing, and 12 weekly telephone goal reinforcement calls (3 months). Control subjects will receive verbal lifestyle advice only. Feasibility will be assessed through recruitment and retention. Qualitative evaluation interviews will be conducted with a subsample of 24 purposefully selected participants at 12 months. Assessment for risk factor changes will be measured at pre-intervention and 6 and 12 months. Associations between variables will also be assessed descriptively.

**Discussion:**

Preventive cardiology guidelines highlighted the importance of lifestyle interventions, and lifestyle intervention adherence was proven to reduce atherosclerotic cardiovascular disease (ASCVD) risk, regardless of the individual's genetic risk. Preventive cardiology programmes may fail to adequately support persons in modifying risky behaviours, and research demonstrates that healthy practices among high-risk individuals can remain suboptimal.

Siblings and offspring of patients with premature CHD are at increased risk of ASCVD. Despite this, there is no process in place for routine screening and support to modify risk. It is hypothesised that participants assigned to the intervention arm will show more cardio-protective lifestyle-related improvement from the baseline than those in the control group. To date, this is the first trial being conducted amongst Maltese first-degree relatives. This study addresses the needed research, and the results will inform a definitive trial.

The funding institution is the University of Malta.

**Trial registration:**

ISRCTN, ISRCTN21559170; Registered 06/08/2020,

## Background and rationale

An important risk factor for atherosclerotic cardiovascular disease (ASCVD) development is family history [1]. A subset of ASCVD is coronary heart disease (CHD). The risk of having a CHD event is increased in the families of affected patients who had a premature atherosclerotic event [2], defined as an event occurring in males before 55 years and before 65 years in females [3]. In Malta, about 40% of cardiac patients will present with premature CHD [4]. First-degree relatives, such as siblings of patients with premature CHD, have an increased risk of developing the disease themselves by approximately 40%, while offspring of patients with premature CHD have about a 60% to 75% increased risk when compared with the general population [5]. Moreover, the risk is higher in males than in females [6, 7] and more substantial in middle-aged persons [8]; it increases with the number of affected relatives [5, 9] and even more so if the diseased vessel is a main left coronary artery [10].

Siblings and offspring of CHD patients are also more likely to have a higher prevalence of central obesity (≥102cm in Europid men; ≥88 cm in Europid women), hypertension, hypercholesterolemia, and smoking than people who do not have a first-degree relative with CHD [11–14]. In turn, these outcomes can concurrently act as determinants for subsequent CHD events [3, 15]; however, they can be modified or controlled. Preventive cardiology guidelines highlighted the importance of lifestyle interventions [3, 16]. Research shows that smoking cessation [17–20], adherence to a Mediterranean diet, and physical activities reduce ASCVD incidence and mortality [21–23]. Also, adherence to a Mediterranean diet and physical activity reduce risk regardless of the individual's genetic risk [24–28]. However, a gap between scientific evidence and clinical practice exists, and current prevention programmes do not support individuals with a strong family history in identifying and modifying their risk. Primary prevention is essential among individuals at increased risk [3, 16].

A recent systematic review with a meta-analysis of preventive programmes highlighted the application of counselling elements to help individuals improve their heart health risk [29]. These identified elements included: compassion, listening, affirmation, evocation, use of open questions, summarising and resolving ambivalence. Such elements could be combined with educational resources. Barrier change identification and goal setting were also identified as essential elements. It was also suggested that the application of Motivational Interviewing (MI) communication skills; open-ended questions, affirmation, reflection and summarisation (OARS), could be combined with the application of ASCVD risk scores [29]. Although a recent meta-analysis using risk scores in primary prevention efforts showed no evidence in reducing ASCVD event outcomes, this could be explained by the low event rate in individuals without pre-existent ASCVD. Therefore, it may not be feasible or practical to conduct a large trial to evaluate ASCVD risk calculators' effectiveness in reducing ASCVD outcomes [30]. However, it would be more practical to focus on modifiable risk factor change or adherence to lifestyle therapies. It is necessary to conduct further research to evaluate factors that enable and motivate individuals at risk, yet without symptomatic pre-existent ASCVD, to support them in adopting healthy lifestyle changes [29, 31].

This approach could be ideal amongst first-degree relatives of patients with premature ASCVD. Risk factor evaluation, education, and communication using counselling elements and risk scores may help establish a successful cardiovascular risk factor change.

## Aim and objectives

This study aims to evaluate a pilot study of a preventive cardiology program designed to promote risk reduction in a sample of asymptomatic first-degree relatives of patients with premature CHD.

Primary objectives are as follows:
Feasibility: To assess the recruitment processes and study uptake to inform the feasibility of a large-scale randomised controlled trialAcceptability: To determine whether the Intervention for risk reduction is acceptable by first-degree relatives

Secondary objectives are as follows:
3.Potential effectiveness: To determine if the programme provides preliminary evidence for modifying lifestyle behaviours; physiological, anthropometric, biochemical parameters; Heart Age (estimated age based on ASCVD risk); and health literacy4.Association between variables: To determine if the programme provides preliminary evidence for an association with lifestyle factors such as Mediterranean diet and physical activity, which themselves can act as determinants to clinical outcomes such as BMI/WC/lipids/blood pressure/HbA1c.

## Methods/design

### Setting

ASCVD risk evaluation, delivery of Intervention, and outcome measurements are being carried out from an outpatient clinic based at the Malta General State Academic Hospital.

### Study type and design

The study is an interventional pilot study. The design consists of a single-centre, 2-group pilot trial consisting of a target sample of 100 first-degree relatives. This design was chosen to determine the association with and effectiveness in addressing the modifiable cardiovascular risk factors. Qualitative evaluation interviews will be conducted with a subsample of 24 purposefully selected participants at 1 year. In this way, quantitative and qualitative data strengthen the study, allowing it to achieve all its proposed objectives [32]. More information about the study is available on a registry platform (*http://www.isrctn.com/ISRCTN21559170*).

### Materials

#### Sociodemographic questionnaire

A questionnaire was designed to collect sociodemographic data, including questions on age, sex, educational level, employment status, time of the patient coronary event, and whether participants live alone or live with others. These variables will be collected to characterise the sample. However, as randomisation is not guaranteed to result in perfectly balanced groups at baseline, variables that may be associated with the outcome will be checked for balance and controlled for in subsequent analysis if necessary.

### Primary outcomes

#### Feasibility

Feasibility will be ascertained by evaluating the recruitment and intervention processes. The study's feasibility requires that the Intervention be effectively carried out amongst an adequate number of first-degree relatives over 2 years. The assessment of the feasibility of the recruitment process will include records of the number of first-degree relatives:
Reached via patients/ video clip (link to video clip)/ poster (link to poster)/ study participants/ clinician,Who expressed interest in the study,Who are potentially eligible, with reasons for ineligibility,Who agreed to participate in the trial,Lost to follow-up (retention and drop-out rate),

Furthermore, the assessment of the feasibility of the Intervention will include the time taken to:
Complete the cardiovascular risk assessment,Deliver the Intervention (in-person session and telephone sessions).

#### Acceptability

Acceptability will be evaluated by determining how well the Intervention is received by first-degree relatives and the extent to which this Intervention could meet their needs. Post-intervention questionnaires and interviews will be used to collect this data. This requires data of the participants' most valued intervention components in terms of being supportive and the participants' views of the quality of interactions during intervention sessions, along with how well the intervention targets can be incorporated into participants' lifestyles, taking into consideration any difficulties participants might have experienced while attempting to comply with the programme goals. We will evaluate the internal reliability (i.e. internal consistency) of self-produced questionnaires during the piloting process using Cronbach’s alpha scores to identify any items that respondents are not answering consistently with their responses to other items before general implementation. We will calculate the alpha reliability value for the whole scale and will also infer individual item reliability via alpha values calculated for the scale with each item deleted in turn. Any items identified as detracting from overall reliability will be considered for removal or re-wording and re-piloted if necessary until satisfactory scale reliability is achieved.

### Secondary outcomes

#### Potential intervention effectiveness

Preliminary evidence for the effect of the intervention will be determined by an increase in the mean smoking cessation attempts, increased mean Mediterranean diet score, and physical activity level. A decrease in the mean serum lipids, blood pressure level, waist circumference, and body mass index, and Heart Age will be considered as improvements in cardiovascular risk factors if statistically significant. Any trends identified across variable results will be explored.

The following are secondary outcome measurements considered:
Smoking status

Smoking status will be answered by a 'yes' or 'no.' As self-reporting depends on participants' honesty, those who report that they have stopped smoking will be tested for expired carbon monoxide using a carbon monoxide monitor.
Mediterranean diet score

The 14-point Mediterranean Diet Adherence Screener (MEDAS) [33] is a fourteen-item questionnaire that assesses adherence to the Mediterranean diet with two 'yes-or-no' questions on food intake habits and another twelve questions on food consumption frequency. The questionnaire is based on the nine-item index used in the PREDIMED study, and it covers the use of Mediterranean diet habits and frequency of consumption of Mediterranean food items. If the item/question is not met, a score of zero will be recorded. Therefore, the final score will range from 0 to 14. The higher the score, the greater the adherence to the Mediterranean diet.
Physical activity level

The rapid assessment of physical activity (RAPA) questionnaire is a 9-item valid questionnaire, which requires 2 to 5 min to complete [34]. The questionnaire is based on the Centres for Disease Control and Prevention (CDC) guidelines, suggesting a minimum of 30 min of moderate physical activity daily. The questionnaire covers a range of physical activity levels, from sedentary to regular vigorous physical activity and strength training and flexibility. The total score of the first seven items is one score for each and, thus, scoring is from 0 to 7 points. Responses to strength training and flexibility items are scored separately, with strength training = 1 point, flexibility = 2 points, or both = 3 points. Therefore, the final score would range from 0 to 10.
Biochemical measures

Blood biochemicals (lipids, HbA1c) will be analysed using the Roche COBAS analyser, while TFT will be analysed using the Siemens ADVIA Centaur analyser. Both analysers are closed systems, and the kits that will be used are only those provided by Roche and Siemens, respectively.
Physiological measures

Resting physiological measurements will be measured using an Omron™ blood pressure monitor, measured two to three times by auscultation, and an average will be taken as the final measurement. Heart rate shall be measured manually using the radial pulse. For both measurements, the first measurement shall be monitored after a 10-min seated rest, repeated 10 min after, and then again at the end of the session. Blood pressure will be measured in both arms.
Anthropometric measures

Anthropometric measurements will be measured using a SECA scale with a height gauge. Numerous steps will be taken to avoid measurement errors. Weight will be taken to the nearest 0.1 kg and both measurements recorded twice. Recording of the waist circumference will be recorded while the participant is standing. A non-elastic measuring tape will be placed at the midpoint between the iliac crest and the lowest rib and at the umbilicus level. This measurement will be taken at the end of expiration.
Heart Age

Heart Age will be calculated after obtaining the following parameters: age, sex, systolic blood pressure, cholesterol, smoking status, weight, and height. The parameter data obtained will be inputted into the online calculator to generate a score. This score will allow for the observation of changes in global risk [35].
Health literacy

The Health Literacy Questionnaire (HLQ) has nine scales in total [36, 37]. We decided to select those scales which we think are relevant to the Intervention. The questions will not be amended as they are validated in the way they are. However, the researcher shall tell the participant that the questions asked are about their heart health.

The scales selected are: scale 1, Feeling understood and supported by healthcare professionals; scale 2, Having sufficient information to manage health; scale 3, Actively managing health.

The selected scales' response options range from 1 to 4, with the scoring as follows: 'strongly disagree’ = 1, 'disagree’ = 2, 'agree' = 3, 'strongly agree’ = 4. The total score is calculated for all the questions on that scale and divided by the number of items.

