#### Recruitment method for interviews

All the intervention participants will be asked to complete a questionnaire at the end of the programme.

From a sample of first-degree relatives who completed the programme, 24 individuals will be asked to participate in the interviews. A stratified purposeful sample will be chosen varying on preselected parameters deemed analytically relevant to the Intervention, providing maximum variation. These are sex, age, and risk profile at 12 months. Participants for whom post-intervention outcomes did not improve and participants who had improved their risk profile at 12 months will be purposively selected for focused analysis to identify the Intervention's strengths and weaknesses [32].

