#### Secondary outcome analysis

##### Objective 3: Estimates of effect and preliminary evidence of efficacy

The likely range of effects will be estimated using liberal confidence intervals. Preliminary estimates of intervention efficacy will be established via hypothesis tests with liberal alpha values (e.g. 0.15, 0.2). Numerical outcomes measured on an interval level, and numerical outcomes measured on an ordinal scale that can be considered approximate to interval level, will be assessed using independent samples t tests. Categorical data will be assessed using the chi-squared test for association.

Intention-to-treat analysis will be used to test for the differences between the two groups at the endpoint [50]. Intention-to-treat analysis is considered the gold standard method for evaluating a new intervention. This method includes all study participants whether or not they have completed the study program and will preserve the randomisation process as it keeps the groups balanced in their number of participants in case of any drop-outs, thus minimising biases [51].

Risk ratios (RRs) will be generated for selected outcome variables, dichotomised as necessary, from proportions of participants meeting particular criteria (e.g. control of blood pressure) in the control and intervention groups.

Effect sizes such as Cohen's d statistics will be calculated for each outcome measure and presented alongside parameter estimates in each group and associated confidence intervals. These, in conjunction with other statistics derived from the pilot analysis, may be used to estimate sample size for a subsequent follow-up RCT [38].

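### Heart Age includes chronological age, so the planned unadjusted endpoint t test is unbiased but less precise than the collected data allow

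*Protocol article*

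**What the plan says.** Under Secondary outcomes (Potential intervention effectiveness), a fall in the means of several risk factors "and Heart Age will be considered as improvements in cardiovascular risk factors if statistically significant". The text does not say whether the fall is relative to baseline or to the control arm.

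The Heart Age paragraph lists the inputs: "Heart Age will be calculated after obtaining the following parameters: age, sex, systolic blood pressure, cholesterol, smoking status, weight, and height". It gives the purpose as follows: "This score will allow for the observation of changes in global risk". Aim and objectives describes Heart Age as an age estimated from ASCVD risk, so it is on a scale of years.

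Objective 3 fixes the analysis. Numerical outcomes on an interval or near-interval scale "will be assessed using independent samples t tests", and "Intention-to-treat analysis will be used to test for the differences between the two groups at the endpoint". It names no change score, baseline term or age term. It adds that Cohen's d will be reported for every outcome and may help to size a later trial.

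Adjustment appears only in the Sociodemographic questionnaire section, where it depends on a check for baseline imbalance. Participants sets a lower age limit of 30 and no upper one. Group randomisation gives 50 per arm.

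**The concern.** Two people with identical modifiable risk factors but ages 20 years apart will have very different Heart Ages. Randomisation balances that difference on average, but it remains in the error term of an unadjusted t test. The planned test therefore measures a treatment effect of perhaps a few years against a spread that includes the full age range of the sample, although each participant's age and baseline Heart Age are already recorded.

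At stake is the width of the interval for the trial's only named global risk score and the use of its effect size in planning. A standardised effect taken from raw Heart Age describes the unadjusted analysis. It would mislead if the next trial were analysed with adjustment.

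A smaller matter is the word decrease. Someone whose risk factors stay constant gains roughly one Heart Age year over 12 months, so a literal fall from baseline is a harder standard than no worsening of risk.

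**Working it through.** The article gives no SD, effect size or power for Heart Age, and Sampling frame says the pilot is not expected to be powered for group differences. There is therefore no stated figure to reproduce, and every SD below is an assumption.

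**Inputs from the article:** 50 per arm; comparison at the endpoint; example alpha values 0.15 and 0.20; follow-up at 6 and 12 months.

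**Assumptions:** Heart Age = age + excess, with age and excess independent and an age slope of 1; SD of age 6 to 12 years; SD of excess 4 to 10 years; true effect 2 years; two-sided alpha 0.20; correlation of excess between baseline and 12 months 0.7.

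**Step 1: variance of raw Heart Age.** SD(raw) = √(SD_age² + SD_excess²). With 10 and 6: √(100 + 36) = 11.66. Age supplies 100/136 = 74% of the variance, and the variance ratio of raw to excess is 136/36 = 3.78.

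**Step 2: standard error of the arm difference.** SE = SD × √(2/50) = SD × 0.2.
- Raw endpoint: 11.66 × 0.2 = 2.33 years.
- Heart Age minus age at the endpoint: 6 × 0.2 = 1.20 years.
- Change from baseline: SD = 6 × √(2 × 0.3) = 4.65, so SE = 0.93 years.
- ANCOVA on baseline Heart Age and age: residual SD = 6 × √(1 − 0.49) = 4.28, so SE = 0.86 years.

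**Step 3: power for 2 years, alpha 0.20.** Raw 0.34; Heart Age minus age 0.65; change about 0.81; ANCOVA about 0.85. The last two come from a 3,000-run simulation, which also gave 0.35 and 0.66 for the first two.

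**Step 4: sensitivity to the assumed SDs** (same effect and alpha).

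| SD age / SD excess | Age share of variance | Variance ratio | Power, raw | Power, Heart Age minus age |
|---|---|---|---|---|
| 6 / 10 | 26% | 1.36 | 0.34 | 0.39 |
| 8 / 10 | 39% | 1.64 | 0.31 | 0.39 |
| 8 / 8 | 50% | 2.00 | 0.35 | 0.49 |
| 8 / 6 | 64% | 2.78 | 0.39 | 0.65 |
| 10 / 6 | 74% | 3.78 | 0.34 | 0.65 |
| 12 / 6 | 80% | 5.00 | 0.30 | 0.65 |
| 12 / 4 | 90% | 10.00 | 0.31 | 0.89 |

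Age supplies at least half the variance whenever its SD is at least that of the excess. At 8/8 the simulated power with ANCOVA was 0.68.

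**Step 5: bias and type I error.** In the simulation at SDs 10/6, the mean between-arm difference was −0.01 for a true 0, −0.99 for a true −1 and −2.03 for a true −2. With no effect, the endpoint t test rejected in 0.203 of runs at alpha 0.20.

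**Step 6: within-arm change.** With no effect, mean Heart Age rose by 0.98 and 0.99 years in the two arms. With a true 1-year benefit, the intervention arm changed by 0.01 years; with a 2-year benefit, by −1.00.

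**Step 7: effect size for planning.** At SDs 10/6, d = 2/11.66 = 0.17 for raw Heart Age and 2/6 = 0.33 for Heart Age minus age. For 80% power at two-sided alpha 0.05, these correspond to 534 and 142 per arm.

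**The case against.** The strongest reply is that nothing here biases the trial. Objective 3 plans a between-arm test, the abstract's hypothesis is also relative to control, and ageing affects both arms alike. Heart Age is one secondary outcome of a pilot whose primary objectives are feasibility and acceptability. Lack of baseline adjustment is a general matter that touches BMI, blood pressure and lipids too, and an analysis plan not shown might settle it. All of this limits the weight of the point. It does not remove it: Objective 3 states a specific test, and that test leaves out age and baseline values already in hand. The imbalance-triggered adjustment does not secure the gain, because the gain in precision does not depend on imbalance.

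Four stronger readings are tempting, and the article does not support them.
- *The criterion penalises every participant for ageing.* This is true only of a fall from baseline within an arm or person. The wording allows that reading, but Objective 3 does not test it.
- *Interview strata will be misclassified.* Recruitment method for interviews says that "participants who had improved their risk profile at 12 months will be purposively selected", but never defines risk profile as Heart Age. The consequence is conditional on that choice.
- *Age dominates the test.* No SDs are given, and age's share runs from 26% to 90% over the assumed grid.
- *Cohen's d will be too small.* A d for raw Heart Age is correctly scaled for raw Heart Age. It misleads only if carried to a trial with an adjusted analysis.

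It is also fair to say that subtracting age is not the main remedy. When everyone ages equally, change in Heart Age and change in Heart Age minus age give the same t test, and baseline adjustment recovers more precision than subtraction alone.

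**Conclusion.** The point holds as one of avoidable imprecision. The planned endpoint t test on raw Heart Age is unbiased and keeps its type I error, but it carries between-person age variance that the recorded data could remove. At assumed SDs of 10 and 6 years, the standard error is 2.33 years against 1.20 for Heart Age minus age and 0.86 with ANCOVA. If excess varies more than age does (6/10), subtraction alone raises power only from 0.34 to 0.39. These figures rest on independence, an age slope of 1, the assumed SDs and, for ANCOVA, the assumed correlation of 0.7.

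The ageing effect is a question of wording, relevant only where Heart Age describes change within an arm or person. For a secondary outcome of a pilot, the importance is minor to moderate. It is worth correcting because the remedy is nearly free and the article says its effect sizes may inform the next trial.

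**What to change.** 1. In Objective 3, prespecify the between-arm comparison of 12-month Heart Age by ANCOVA, adjusted for baseline Heart Age and age regardless of any balance check. An acceptable alternative is Heart Age minus actual age at the same visit, adjusted for its baseline value.
2. Report the adjusted difference, its interval and the residual SD. Use those for planning, and state which analysis any standardised effect belongs to.
3. In Potential intervention effectiveness, state that improvement in Heart Age means a difference between arms, not a fall from baseline within an arm.
4. Wherever Heart Age is used to describe change within a person, including interview selection if risk profile is to rest on it, use Heart Age minus current age.

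The cost is a few sentences and one regression model. Age and Heart Age are already collected, and the model uses two further degrees of freedom out of about 98.
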